### Human subject recruitment

The Emory Transplant Center at EUH will announce an OLT case via encrypted email and/or private phone call to the PI, typically 24–48 hours before transplantation. The PI will disseminate this information to study team members involved in screening patient eligibility and obtaining informed consent. Patients will be screened for study eligibility via manual electronic medical record chart review. Eligible patients will then be recruited for study enrollment in their respective location, either the hospital ward, intensive care unit (ICU), or pre-operative holding area. The study team will obtain informed consent by reviewing the study purpose, protocol, possible risks and benefits, right to refuse to partake, and right to withdraw in a confidential space. The patient or their legal representative will be given time to ask questions and have their questions answered in a satisfactory manner. Eligible subjects will be ensured their medical care does not change whether they participate in the study or not. If the subject agrees to participate, he or she will provide written informed consent per accordance with the ethical principles from the Declaration of Helsinki.

### Procedures

This study was approved by the Emory University institutional review board (IRB), protocol number 5728. Study enrollment began on August 1, 2023. At the time of publication, this study has enrolled thirty-four patients and no data analysis has been performed. A serum lab protocol capturing PaO_2_ on serial arterial blood gas (ABG) analysis, other standard of care (SOC) tests, and cytokine, protein, and HIF-1α (biomarker) levels via serum biosample collection was implemented “Table 5.” Peri-reperfusion serial ABG will be obtained ~30 minutes before through ~2 hours after reperfusion within the SOC.

**Table 5 pone.0301281.t005:** Subject serum lab evaluation timeline.

Time Point	Serum Laboratory Values
Admission	CMP, CBC, INR, Fibrinogen (SOC)
After anesthesia induction	Biomarker Panel
Peri-reperfusion	Serial ABG (SOC)
~2 hours after reperfusion	Biomarker Panel
~48 hours after reperfusion	Biomarker Panel
Postoperative day 2	CMP (SOC)
Postoperative day 7	INR, Bilirubin, AST/ALT (SOC)
Postoperative days 1–7	Serial AST/ALT (SOC)

CMP indicates complete metabolic panel; CBC, complete blood count; INR, international normalized ratio; SOC, standard of care; ABG, arterial blood gas; AST, aspartate aminotransferase; ALT, alanine transaminase. *The study team will only collect biosamples for the biomarker panel*.

The study team will collect peripheral serum biosamples at planned intervals to test the biomarker panel. Biosamples will be obtained via an arterial line, placed preoperatively as a SOC procedure. All intraoperative serum biosamples will be obtained by the anesthesiologist. All postoperative serum biosamples will be drawn by the ICU or inpatient floor nurse. The other tests are SOC and will be obtained and analyzed in their usual fashion. Extra labs will be obtained at the discretion of the anesthesiologist or intensivist within the SOC.

At each time point outlined for biosample collection, about 12 mL of blood will be collected into 2 edetic acid (EDTA) tubes (about 6 mL in each tube). Each subject will have 3 blood draws, about 36 mL of blood collected in total. Within 30 minutes of collection, serum biosamples will be processed via centrifugation at 4°C at 2,000g for 20 minutes to separate the plasma from the blood cells. The upper layer of plasma will be transferred via pipet to 1.5 mL cryovials. Upon centrifuging, every 4 mL of blood makes about 2 mL of centrifuged plasma. Thus, 12 mL of blood should make about 6 mL of centrifuged plasma, which will then be aliquoted to four 1.5 mL cryovials. A summary of serum biosample collection and processing is in “Table 6.” All tubes and cryovials will be labeled with the date and time of collection, protocol number, study identification number, and timepoint letter. Biosamples will be stored in a -80° freezer in the laboratory for later batch analysis. Standard kits to test these biomarkers, including Meso Scale Discovery Assay kits and multiplex ELISA, will be performed in duplicate in a laboratory per standardized manufacturer guidelines.

**Table 6 pone.0301281.t006:** Summary of serum biosample collection and processing.

Timepoint	Timepoint Letter	Patient Location	Source	Biosample and Tubes	Samples Stored
After Induction of General Anesthesia	A	OR	Peripheral Blood	~12 mL total (~6 mL in 2 purple top EDTA tubes)	4 cryovials of EDTA plasma (1.5 mL each)
2 Hours after Reperfusion	B	OR	Peripheral Blood	~12 mL total (~6 mL in 2 purple top EDTA tubes)	4 cryovials of EDTA plasma (1.5 mL each)
48 Hours after Reperfusion	C	ICU or Inpatient Floor	Peripheral Blood	~12 mL total (~6 mL in 2 purple top EDTA tubes)	4 cryovials of EDTA plasma (1.5 mL each)

EDTA indicates edetic acid.

### Data collection and management

Participants will be followed for up to 30 days with weekly capture of clinical data extracted from the electronic medical record. Key clinical, laboratory, and radiology results will be accessed within the electronic medical record. Collected data will include relevant exposures, covariates, and outcomes. Covariates include known risk factors for EAD, peri-reperfusion anesthesiologist-administered FiO_2_, peri-operative immunosuppressive agents, and the use of NRP and/or allograft machine perfusion. Biosamples will be labeled with the date, time, study protocol number, study identification number, and timepoint. Data will be stored in an encrypted, password-protected, de-identified database for the duration of the study and as per institutional and journal publication policies. Biosamples will be banked and managed per institutional policy. Only the PI will have access to a restricted, password-protected file which lists study identification numbers to corresponding participant identifiers and biosample information. Only the study personnel will have access to the long-term laboratory freezer storing the biosamples. The study team will only have access to the de-identified database. Data analysis will be performed with the de-identified dataset only.

### Statistical analysis

Patient and transplant characteristics will be reported descriptively (median and range or proportions). Patients will be grouped by the development of EAD or non-EAD. A type I error of 0.05 will be used as the criterion for statistical significance. Analyses will be performed using the R project for statistical computing.

For aim one, the proportion of patients exposed to hyperoxemia in each group, EAD or non-EAD, will be compared. Values will be presented as the median with interquartile range (IQR) or mean with standard deviation (SD) for continuous variables as appropriate and as the total number (percentage) for categorical variables. Comparisons between groups will be made using the Student’s t test or Mann-Whitney U test for continuous variables and chi-square test or Fisher’s exact test for categorical variables as appropriate. A multivariate logistic regression analysis will be performed with other EAD risk factors (e.g., donor type and age, ischemia time, and MELD score).

For aim two, cytokine, protein, and HIF-1α levels will be compared between the two groups, EAD and non-EAD, using analysis of variance (ANOVA) with Tukey’s adjustment for *p*-values at each time point and over multiple time points. For each biomarker, patients will be categorized into quartiles based on measured concentration, and the odds ratio for EAD will be compared among quartiles using a logistic regression analysis. The lowest quartile for proinflammatory cytokines (or highest quartile for anti-inflammatory cytokines) will be used as the reference group to calculate adjusted and unadjusted odds ratios for EAD. We will develop a logistic regression model of EAD as a function of inflammation, using the area under the receiver operating characteristic (ROC) curve and the Hosmer-Lemeshow goodness-of-fit test to assess model discrimination and calibration, respectively. We will perform a subset analysis to determine whether peri-reperfusion hyperoxemia, compared to non-hyperoxemia, alters their pattern of expression.

NRP during DCD and machine perfusion of the allograft during storage, which limit ischemia and allow early re-exposure to oxygen, are associated with a reduced incidence of EAD and improved postoperative outcomes [41–45]. Consequently, patients who receive an allograft that underwent NRP or stored on a machine perfusion pump will be analyzed separately from those who receive an allograft stored via static cold storage, the conventional and most widely used method of allograft storage worldwide. At our institution, only a small portion of allografts undergo NRP and normothermic machine perfusion is predominately used for DCD allografts that did not undergo NRP. Thus, DCD allografts at our institution either undergo NRP or are placed on a normothermic machine perfusion pump, but not both.

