## Methods

### Study aims

Our central hypothesis is peri-reperfusion hyperoxemia and immune dysregulation exacerbate IRI and increase the risk of EAD. Our first aim is to determine the association between peri-reperfusion hyperoxemia and EAD after deceased donor OLT. We will examine peri-reperfusion median serum PaO_2_ levels to determine the odds EAD develops in patients exposed to hyperoxemia compared to those not exposed. Our second aim is to evaluate whether peri-reperfusion perturbed cytokine, protein, and HIF-1α levels correlate with EAD after OLT. We will measure peri-reperfusion serum cytokine, protein, and HIF-1α levels before and 2 and 48 hours after reperfusion for comparison between those who develop EAD and those who do not using the same participants from aim one. We will perform a subset analysis to determine whether peri-reperfusion hyperoxemia, compared to non-hyperoxemia, alters their pattern of expression.

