### Sample size calculation

A total enrollment of 40 participants is planned. A post-hoc power analysis was performed based on exploratory data from Friedman et al. using the estimated mean and standard deviation (SD) of IL-8 on day 1 in the EAD and non-EAD groups to calculate effect size [34]. Since only median values and IQR were available, mean and SD of IL-8 for each group were estimated as median and IQR/1.35, respectively. A two tail post-hoc power analysis using an effect size of 0.717, alpha of 0.1, EAD sample size of 29, and non-EAD sample size of 44 achieved 84% power. To achieve power of 70% (A priori) with the same parameters, a total sample size of 40 is needed with at least 20 in each group. Given the pilot design of this study, a total sample size of 40 patients will be enrolled to generate preliminary data. This is feasible as our institution performs an average of 118 adult deceased donor OLT cases per year (Organ Procurement and Transplantation Network [OPTN], 2012–2021 data). Efforts will be made to enroll all eligible participants. There is no pre-determined percentage of subjects according to sex, gender, race, or ethnicity.

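### Aim two's ANOVA across the three sampling times names no patient or repeated-measures term; run literally, its time-averaged group test rejects too often and its group-by-time test too rarely

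*Protocol article*

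**What the plan says.** The Statistical analysis section names one method for comparing biomarker levels between the EAD and non-EAD groups in aim two, "using analysis of variance (ANOVA) with Tukey’s adjustment for *p*-values at each time point and over multiple time points". One clause thus covers two analyses: a comparison within each sampling time and a comparison across sampling times. The significance criterion is also given there: "A type I error of 0.05 will be used as the criterion for statistical significance".

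The data structure is set out elsewhere in the article. Study aims says that levels are measured "before and 2 and 48 hours after reperfusion for comparison between those who develop EAD and those who do not". Procedures says "Each subject will have 3 blood draws, about 36 mL of blood collected in total", and Table 6 labels the draws A (after induction), B (2 hours) and C (48 hours). Sample size calculation adds "A total enrollment of 40 participants is planned".

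Nowhere does the article mention repeated measures, a patient effect, a mixed model or correlation within patients. Nor does it say that the ANOVA is an ordinary one, which error term it uses, or that values are treated as independent.

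**The concern.** Three values from one patient are normally correlated. EAD status differs only between patients, so a group comparison averaged over time must be judged against between-patient variation. Group-by-time divergence is seen within patients and must be judged against within-patient variation. An ANOVA without a patient term uses one pooled residual for both. That residual is too small for the first test and too large for the second.

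At a single sampling time each patient gives one value, so an ordinary ANOVA is right there. The sentence carries the same method over to the across-time analysis without adding anything. The Tukey step does not help: with two groups at one time there is only one contrast, so it changes nothing, and across group-by-time cells its standard form assumes independent cell means.

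At stake are the p-values of the across-time comparison for each of the 13 biomarkers in Table 4. Overall group differences would be declared too often, and courses that start alike and diverge after reperfusion would be detected too rarely.

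**Working it through.** **Inputs.** From the article: 40 patients, 3 samples each (at most 40 × 3 = 120 values per biomarker), alpha 0.05, effect size 0.717 SD (Sample size calculation), and EAD in 20-25% of recipients (Introduction), that is 8 to 10 of 40. Assumed: within-patient correlation rho, equal for all pairs of samples, from 0.1 to 0.7; normal data; two-sided group tests.

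**The plan's own figure.** With d = 0.717, two-sided alpha 0.1 and 20 per group, the noncentral t distribution gives 72.0% power, and 20 per group is the smallest size reaching 70%. The stated total of 40 reproduces.

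**Group effect averaged over time, pooled error.** The variance of a patient's three-sample mean is σ²(1 + 2rho)/3. Treating the values as independent makes it σ²/3, too small by the factor 1 + 2rho. The large-sample rejection rate under the null is 2 × [1 − Φ(1.96/√(1 + 2rho))]:

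| rho | 1 + 2rho | Formula | Simulation, pooled error | Simulation, patient-level error |
|---|---|---|---|---|
| 0.1 | 1.2 | 7.4% | about 7% | about 5% |
| 0.3 | 1.6 | 12.1% | about 12% | about 5% |
| 0.5 | 2.0 | 16.6% | 16-17% | about 5% |
| 0.7 | 2.4 | 20.6% | 20-21% | about 5% |

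The simulations used at least 20,000 runs per setting, with 114 error degrees of freedom for the pooled test (120 values less 6 cell means) and 38 for the patient-level test. Results barely change between 20/20, 10/30 and 8/32 splits. With correlation that decays over successive samples (first-order autoregressive, 20/20), the pooled rates are 14.5% at 0.5 and 19.3% at 0.7. At rho = 0 there is no inflation.

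**Group-by-time, pooled error.** The right error variance is σ²(1 − rho), but the pooled residual is about σ². Under the null the pooled test rejects in about 1.5%, 0.4% and under 0.1% of runs at rho 0.3, 0.5 and 0.7 (20/20).

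For power, take differences of 0, 0.717 and 0.717 SD at samples A, B and C with a 10/30 split. The mean difference is 0.478, so the squared deviations sum to 0.478² + 2 × 0.239² = 0.343. Multiplying by 10 × 30/40 = 7.5 gives 2.57, and the noncentrality of the correct test is 2.57/(1 − rho) = 3.67, 5.14 and 8.57. The noncentral F with 2 and 76 degrees of freedom gives 37%, 50% and 73%, in line with the simulated values:

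| rho | Pooled error | Within-patient error | Share of power lost |
|---|---|---|---|
| 0.3 | 21% | 37% | 1 − 21/37 = 43% |
| 0.5 | 15% | 49% | 1 − 15/49 = 69% |
| 0.7 | 9% | 72% | 1 − 9/72 = 88% |

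**Tukey contrasts between groups at the same time.** With pooled error and Tukey's adjustment over the six group-by-time cells, the chance under the null that any same-time EAD versus non-EAD contrast is significant is about 1.2-1.5% at every rho from 0 to 0.7. These contrasts are not inflated.

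**The case against.** The strongest reply is that the fault is not in the text. An ANOVA across times, set beside one at each time, fits a repeated-measures ANOVA as well as an ordinary one. Study aims shows that the authors know the same participants supply every sample, and an article commonly leaves the error term and covariance structure to the full protocol or SAP. This largely stands. A reader might infer that the article states an ordinary ANOVA on 120 independent values. It does not, so the error rates above are conditional on a literal reading.

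A reader might also infer that every across-time p-value would be inflated. The documents do not support that either: the excess falls on the time-averaged group effect, while Tukey contrasts between the groups at the same time stay below 5%.

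Third, one might conclude that divergence after reperfusion would mostly be missed. The group-by-time test loses more than half its power only from rho of about 0.5. Moreover, the comparisons at each time point, in the same sentence, test samples B and C directly and are valid on this count. In the scenario above each has about 48% power at alpha 0.05, unadjusted.

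Finally, the correlation is unknown. The Discussion gives reasons why it could be weak: immunosuppression changes between samples, and transfusion may dilute the markers. The count of 120 is an upper bound, because recipients of NRP or machine-perfused grafts are analysed separately from static cold storage.

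What remains is that the article names the test and its adjustment, and the named method, taken as it stands, does not match the stated data structure. Any positive correlation shifts both tests in the directions shown, in any storage subgroup.

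**Conclusion.** The point holds as a conditional one. The across-time analysis of aim two names no patient or repeated-measures term for data with three values per patient. Run literally with pooled error, the time-averaged EAD test has a true size of about 7% to 21% for rho from 0.1 to 0.7, and the group-by-time test is conservative, with the power losses shown. These figures rest on an assumed and equal within-patient correlation, normal data, and all 40 patients in one analysis. The aim-two comparisons at single time points are unaffected. If a repeated-measures analysis was intended, the defect is one of wording, but it still needs correcting because the validity of these p-values depends on it.

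**What to change.** For the across-time analysis of each biomarker, replace the stated ANOVA with a linear mixed model, or a repeated-measures ANOVA. Use EAD group, time and group-by-time as fixed effects and a patient effect (a random intercept, or an unstructured covariance over the three samples), with small-sample degrees of freedom such as Kenward-Roger or Satterthwaite. Take the EAD contrasts at 2 and 48 hours and the group-by-time test from that model. If this was already the intention, say so in the text.

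The cost is one sentence and standard R code, with no new patients or samples. The Procedures section reports that no analysis had been done at publication, so the change could be made before results are seen. The downside is that some p-values for the group main effect will be larger.

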### Eligibility criteria

Inclusion criteria include age ≥ 18 years, end-stage liver disease, and donation after brain or circulatory death. Exclusion criteria include living donor donation, repeat OLT within a week of transplantation, multiple organ transplantation, and pregnancy or lactating patients. Eligibility criteria are summarized in “Table 2.” Prisoners do not meet criteria for OLT at our institution and are not included in this study. Donors after circulatory death who undergo NRP, a form of mechanical circulatory support similar to extracorporeal membrane oxygenation which restores oxygenated blood flow to the allograft after cardiac arrest and attenuates ischemic injury before recovery, will be included in the study. Patients who receive an allograft maintained on machine perfusion during storage, which re-exposes the allograft to oxygen before implantation, will also be included in the study. To limit the early re-exposure to oxygen as a confounding variable, these patients will be analyzed separately from those who receive an allograft maintained in static cold storage, the conventional method of allograft storage.

**Table 2 pone.0301281.t002:** Eligibility criteria.

Inclusion Criteria	Exclusion Criteria
Age ≥ 18 years	Living donor donation
End-stage liver disease	Repeat OLT within a week of transplantation
Donation after brain death	Multiple organ transplantation
Donation after circulatory death	Pregnancy or lactating patients

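### On the centre's stated practice, donor type is constant in the separate cold-storage analysis, and the 70% power at 40 patients belongs to neither separate analysis

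*Protocol article*

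**What the plan says.** All statements are in the protocol article.

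- **Split.** Eligibility criteria admits both brain-death and circulatory-death (DCD) donors, with or without perfusion. It says of recipients of perfused grafts that "these patients will be analyzed separately from those who receive an allograft maintained in static cold storage". Statistical analysis repeats this and does not limit it to one aim.
- **Where DCD grafts fall.** Statistical analysis describes local practice: "Thus, DCD allografts at our institution either undergo NRP or are placed on a normothermic machine perfusion pump, but not both". It adds that NRP is used for a small share of grafts and that normothermic machine perfusion is mainly for DCD grafts without NRP. The study has one centre.
- **Adjustment.** The aim-one logistic regression is to include "other EAD risk factors (e.g., donor type and age, ischemia time, and MELD score"). The section does not say in which set this regression is run.
- **Size.** Sample size calculation says "A total enrollment of 40 participants is planned". For 70% power, "a total sample size of 40 is needed with at least 20 in each group". The effect size of 0.717 comes from IL-8 on day 1, and alpha is 0.1. No allowance is made for the split.

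**The concern.** Taken together, the split and the local practice place every DCD graft in the perfused set. The cold-storage analysis then has no variation in donor type, so the first-named example adjuster does nothing there. In the perfused set donor type is nearly constant, since NRP is described only for DCD donors and machine perfusion is mainly used for them. In a pooled model donor type and perfusion carry almost the same information. The plan thus describes no set in which a donor-type coefficient would be informative, and it does not say which set the adjusted model uses. Leaving that open allows a choice between pooled and separate models after the data are seen.

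Separately, the stated power is for 40 patients compared in one analysis. Each perfused graft enrolled takes a patient out of the cold-storage set, so the stated figure is not what either separate analysis delivers.

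**Working it through.** **1. Donor type in the cold-storage set**

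The stated practice gives 0 DCD grafts in this set. A model with an intercept, hyperoxemia, donor type, donor age, ischemia time and MELD score has 6 columns. With donor type constant, a check of the design matrix gives rank 5. The donor-type coefficient is not estimable. The other five, including hyperoxemia, are unaffected by this.

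**2. The plan's own sample size**

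Inputs from Sample size calculation: d = 0.717, two-sided alpha 0.1, 20 + 20 patients. For a two-sample t test,

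- degrees of freedom = n1 + n2 − 2
- noncentrality λ = d × √(n1·n2/(n1 + n2))
- power = probability that a noncentral t with these values lies beyond ± the central t critical value.

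For 20 + 20: λ = 0.717 × √10 = 2.267 and power is 72.0%. For 19 + 19 it is 69.97%. So 40 is the smallest total of two equal groups that reaches 70%, and the stated size reproduces.

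**3. Power in the cold-storage set**

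The document gives no perfused share, so the share s is an assumption. The set size is 40 × (1 − s). Everything else stays as in step 2, including equal groups.

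| Assumed perfused share | Cold-storage patients | λ | Power |
|---|---|---|---|
| 0% | 40 | 2.267 | 72.0% |
| 10% | 36 | 2.151 | 67.8% |
| 20% | 32 | 2.028 | 63.2% |
| 30% | 28 | 1.897 | 58.0% |
| 40% | 24 | 1.756 | 52.3% |

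**4. The perfused set**

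The same shares leave 4 to 16 patients. At the 20–25% incidence of early allograft dysfunction (EAD) given in the Introduction, that is between 4 × 0.20 = 0.8 and 16 × 0.25 = 4 events. It may be fewer, because Statistical analysis says perfusion is associated with less EAD.

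**5. Separating the split from two other issues**

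Statistical analysis sets alpha at 0.05 ("A type I error of 0.05 will be used as the criterion for statistical significance"), and 20–25% EAD in 40 patients means 8–10 cases, not 20. With d = 0.717, alpha 0.05 and 20–25% EAD:

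| Set | EAD / non-EAD | Power |
|---|---|---|
| All 40, no split | 8/32 to 10/30 | 42–48% |
| 32 patients | 6/26 to 8/24 | 34–40% |
| 24 patients | 5/19 to 6/18 | 28–31% |

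Alpha and incidence alone take power from 72% to 42–48%, a loss of 24–30 points. The split then costs a further 8–9 points at a 20% share and about 15–18 points at 40%.

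**The case against.** Several points on the other side stand.

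- **The model does not fail.** A reader might infer that the cold-storage regression cannot be fitted. The document does not support that. Donor type is only an example in the covariate list, the regression is not confined to the cold-storage set, and R would drop a constant column and still estimate the hyperoxemia effect. Restricting to cold storage also removes donor-type confounding by design.
- **The shortfall is of unknown size.** A reader might infer that the analysed sample is far below 40. No perfused share is given; at 10% the set is 36.
- **The low power is mostly not due to the split.** Comparing 28–40% with the planned 70% would charge the alpha mismatch and the EAD incidence to this point.
- **The power concerns aim two.** The effect size is for IL-8, so step 3 says nothing about fitting the aim-one model.
- **The covariate list is not a contradiction.** Data collection and management lists "and the use of NRP and/or allograft machine perfusion" among covariates. That might be read as implying a pooled model, but the section covers what is recorded, and perfusion must be recorded to separate the patients at all.
- **Practice is not a rule.** That no DCD graft is cold-stored describes the centre's practice; eligibility does not require it.
- **It is a pilot.** The Discussion concedes possible low power. A general caution, however, does not correct a specific power figure tied to the wrong number of patients.

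**Conclusion.** The point holds in limited form. On the centre's stated practice, donor type carries no information in the cold-storage analysis and is nearly redundant with perfusion in a pooled one. The set for the adjusted aim-one model is not named. The 70% power applies to 40 patients analysed together, and so to neither separate analysis once any perfused graft is enrolled. For an assumed perfused share of 10–40%, power in the cold-storage set is 68–52% against 72% for all 40, on the Sample size calculation section's own terms. This rests on the assumed share and on the described practice being followed without exception. Alpha and EAD incidence are separate matters and lower these figures further. What is lost for aim one is a redundant adjuster, not the estimate of interest.

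**What to change.** 1. State in Statistical analysis which set the adjusted aim-one model uses.
2. Drop donor type from the cold-storage model, noting that it is expected to be constant there.
3. Restate the power in Sample size calculation for the expected cold-storage number instead of 40, and give the expected size of both sets.
4. Describe the perfused patients without multivariable modelling if they are few.
5. Optionally, add a secondary pooled model of all 40 with a preservation term (cold storage against NRP or machine perfusion) in place of donor type.

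Whether the pooled model should be primary is for the authors to judge. They separate the groups because early oxygen re-exposure confounds the exposure under study, whereas pooling assumes one PaO2 effect across preservation methods. A cold-storage subset of 24–36 patients, with about 5–9 EAD cases at 20–25%, overlaps the pooled data and is too small to test that assumption.

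The cost is wording and one count. Procedures reports thirty-four patients enrolled and no analysis performed, so graft storage can be tallied without looking at outcomes.
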